## Definitions

**Adverse Event (AE):** any untoward medical occurrence in a participant or clinical study participant which does not necessarily have a causal relationship with study treatment or participation.

An AE can therefore be any unfavourable and unintended sign (including an abnormal laboratory finding), symptom, or disease temporally associated with the study treatment or participation (regardless of causality assessments).

**Serious Adverse Event (SAE)** is any untoward medical occurrence or effect that:

- **Results in death**
- **Is life-threatening** – refers to an event in which the participant was at risk of death at the time of the event; it does not refer to an event which hypothetically might have caused death if it were more severe
- **Requires hospitalisation, or prolongation of existing hospitalisation**
- **Results in persistent or significant disability or incapacity**
- Other important medical events\*\*\*.

\*‘life-threatening’ in the definition of ‘serious’ refers to an event in which the patient was at risk of death at the time of the event; it does not refer to an event which hypothetically might have caused death if it were more severe.

\*\*Hospitalisation is defined as an inpatient admission, regardless of length of stay, even if the hospitalisation is a precautionary measure for continued observation. Hospitalisations for a pre-existing condition, including elective procedures that have not worsened, do not constitute an SAE.

\*\*\*Other important medical events May also be considered serious if they jeopardise the participant or require an intervention to prevent one of the above consequences.

**Note:** It is the responsibility of the PI or delegate to grade an event as ‘not serious’ (AE) or ‘serious’ (SAE).

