### 6.4.1 Expected Adverse Events:

|                                           |                                                                                                                                                                                                           |
|-------------------------------------------|-----------------------------------------------------------------------------------------------------------------------------------------------------------------------------------------------------------|
| Mild antidepressant withdrawal symptoms   | Likely to occur in around half of patients reducing and stopping their antidepressants. If mild enough to be tolerated by patient, and short-lived (up to two weeks), these do not need reporting as AEs. |
| Moderate to severe withdrawal symptoms    | If severe or prolonged withdrawal symptoms occur, requiring restarting of antidepressant, please report as related and expected AE.                                                                       |
| Relapse of depression or anxiety disorder | May occur in 10-20% of patients over the one year follow-up, requiring restarting of antidepressant. Please report as related and expected AE.                                                            |

The nature or severity of should be considered when making the assessment of expectedness. If these factors are not consistent with the current information available then the AE should be recorded as 'unexpected'.

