### Baseline telephone screening

Patients will be assessed by telephone and excluded if they have any of the exclusion criteria listed above. Exclusion criteria include significant depressive symptoms despite antidepressant treatment, defined as a score of 12 or more on the Patient Health Questionnaire (PHQ-9) (Kroenke 2001) completed over the telephone. The PHQ-9 is a self-complete questionnaire taking approximately three minutes. It measures nine core symptoms of depression based on Diagnostic and Statistical Manual (DSM-IV) criteria and has high sensitivity and specificity in UK primary care (Gilbody 2007).

Patients will also be excluded if they have significant anxiety at baseline, i.e. a score of 10 or more on the 7-item Generalised Anxiety Disorder scale (GAD-7), also completed over the telephone. The GAD-7 is a brief screening instrument for anxiety also validated in primary care (Spitzer 2006). Though originally developed to detect GAD, it also has good sensitivity and specificity for panic, social anxiety, and post-traumatic stress disorders (Kroenke 2007).

If patients score above 0 (i.e. 1, 2 or 3) on the 9th question of the PHQ-9, about suicide/self-harm, they will be excluded from participating, and this information will be relayed to their GP immediately for them to discuss this, preferably with their permission. The information may be relayed without their permission if necessary, after discussion between the researcher, the principal investigator, and the patient.

If patients are excluded at baseline screening due to either a total PHQ-9 depression score of 12 or more, or a score of 1 or more on the self-harm question 9 of the PHQ-9, or a total GAD-7 anxiety score of 10 or more, and they wish to be reconsidered for inclusion at a later date, they may consent to being recontacted in three months to be re-screened. At re-screening, they may be included in the study if those exclusion criteria no longer apply.

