## Data collection

The outcome measures will be collected at baseline, 3, 6, 9, and 12 months (see table below). Data collection at baseline will be face to face or remotely, but data will be entered on-line using i-survey (University of Southampton secure online survey system) where possible. Data collection at 3 and 9 months will be through either online i-survey, or postal follow-up, with one reminder after two weeks, and subsequent remote, face-to-face or telephone follow-up, to obtain the outcomes for patients who do not complete i-survey or return their questionnaires by post. Postal questionnaires will be accompanied by an explanatory letter requesting return of completed questionnaires within two weeks if possible. Data collection at 6 and 12 months will be remote or face to face. Patient participants will be given a £10 gift voucher for their time at the 6 month assessment.

We will ask participants when we screen them if they are happy to receive texts. If participants are happy to disclose their mobile number we will keep in regular contact with them using the University of Southampton text messaging service. Text messages will be sent to remind participants about appointments and completing online questionnaires. Relevant information on consultations at the practice and use of services outside the practice will also be extracted from patients' medical records by practice staff at the end of the study, assuming they have given consent for this.

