## Consent and data collection summary

| Measure | Reply slip | Screening (telephone) | Baseline (Remote/face to face) | 3 months (postal or on-line) | 6 months (Remote/face to face) | 9 months (postal) | 12 months (Remote/face to face) |
|---------|------------|-----------------------|--------------------------------|------------------------------|--------------------------------|-------------------|---------------------------------|
|---------|------------|-----------------------|--------------------------------|------------------------------|--------------------------------|-------------------|---------------------------------|

|                                                                                                                |   |   |   |   |   | or on-line) |   |
|----------------------------------------------------------------------------------------------------------------|---|---|---|---|---|-------------|---|
| Consent to be contacted about the study                                                                        | ✓ |   |   |   |   |             |   |
| Inclusion/exclusion criteria                                                                                   |   | ✓ |   |   |   |             |   |
| Consent to participate                                                                                         |   |   | ✓ |   |   |             |   |
| Sociodemographics and past history of depression questionnaire                                                 |   |   | ✓ |   |   |             |   |
| Depression (PHQ-9)                                                                                             |   | ✓ | ✓ | ✓ | ✓ | ✓           | ✓ |
| Anxiety (GAD-7)                                                                                                |   | ✓ | ✓ | ✓ | ✓ | ✓           | ✓ |
| Suicidal ideas                                                                                                 |   | ✓ | ✓ | ✓ | ✓ | ✓           | ✓ |
| Discontinuation of antidepressants (for at least 2 months, by 6 months)                                        |   |   |   |   | ✓ |             |   |
| Quality of life (EQ-5D, SF-12)                                                                                 |   |   | ✓ | ✓ | ✓ | ✓           | ✓ |
| Wellbeing (WEMWBS)                                                                                             |   |   | ✓ |   | ✓ |             | ✓ |

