## ETHICAL CONSIDERATIONS

Patients with mental health problems like depression may be more sensitive than others to the demands of participation in research, but the effects of the problems in a primary care population are not so severe as to interfere with patients' capacity to understand the information provided or to give informed consent, provided patients with suicidal ideas, psychotic symptoms, and dementia are excluded. We have ensured the study aims are relevant to patients and the public through PPI input to the design, and their involvement will continue throughout to ensure that participation is voluntary, that easily understood patient information is provided, and fully informed consent obtained. Confidentiality and freedom to drop out at any time (see below) will be ensured.

In obtaining and documenting informed consent, the researcher will comply with applicable regulatory requirements and adhere to the principles of Good Clinical Practice (GCP). Discussion of objectives, risks and inconveniences of the study and the conditions under which it is to be conducted will be provided to the participant by appropriately delegated staff with knowledge in obtaining informed consent and with reference to the patient information leaflet. This information will emphasise that participation in the trial is voluntary and that the participant may withdraw from the trial at any time and for any reason. The participant will be given the opportunity to ask any questions that may arise and provided with the opportunity to discuss the study with family members, friend or an independent healthcare professional outside of the research team and time to consider the information prior to agreeing to participate.

Independent peer review through the NIHR PGfAR panel has ensured scientific quality and rigor. Ethics Committee and HRA approvals will be obtained prior to commencement of work with patients and health professionals, and any subsequent issues will be addressed with the REC or HRA offices as necessary.

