## INDEPENDENT DATA MONITORING COMMITTEE

In addition to the PSC, an IDMC has been set up to oversee trial conduct, chaired by an academic psychiatrist, and including an academic GP, and a senior statistician. The IDMC is tasked with looking at data, statistical and ethical aspects. Serious adverse events will be reported to the IDMC (see below) who will advise about continuation and whether interim analyses are needed. If there is a need to ask for an interim analysis of findings the IDMC will look at them but it would be the PSC who would make the ultimate decision about whether the trial might be stopped, extended or have a substantial change to its protocol.

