#### **4.7 Safety reporting**

A listing of serious adverse events (SAEs) will be provided for all related/unrelated SAEs. If required, a summary table will also be presented.

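### SAP 4.7 plans no by-arm report of suicidal ideas at follow-up, although the protocol schedules them at 3, 6, 9 and 12 months

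*Combined protocol and SAP*

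**What the plan says.** **Schedule.** In the protocol's Consent and data collection summary, the row "Suicidal ideas" is ticked at screening, baseline, 3, 6, 9 and 12 months. The PHQ-9 row is ticked at the same points.

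**Screening.** Under Baseline telephone screening, the rule for a patient scoring 1, 2 or 3 on the ninth PHQ-9 question is: "about suicide/self-harm, they will be excluded from participating, and this information will be relayed to their GP immediately". Such a patient may be re-screened after three months.

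**Planned safety output.** SAP 4.7 reads in full: "A listing of serious adverse events (SAEs) will be provided for all related/unrelated SAEs. If required, a summary table will also be presented". SAP 3.5 adds that tables carry the two group labels.

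**Route into that output.** The protocol's Definitions give the usual seriousness criteria and leave the grading to the principal investigator or a delegate. Of other important medical events they say: "May also be considered serious if they jeopardise the participant or require an intervention to prevent one of the above consequences".

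**Oversight.** The committee section says: "Serious adverse events will be reported to the IDMC (see below) who will advise about continuation and whether interim analyses are needed".

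**The concern.** The trial tests support for stopping antidepressants in patients selected for having no current suicidal ideas. How many in each arm develop such ideas while tapering or afterwards is an obvious safety question, and the protocol arranges to collect the answer four times after baseline. If the SAP is followed exactly, the report will hold SAEs and PHQ-9 totals but no count of patients with suicidal ideas in either arm. Ideation short of an SAE would never be compared between arms, although the data would be on file.

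**Working it through.** The point concerns a missing output, so most of the check is reading. Arithmetic is needed only to judge what the PHQ-9 total could show and what the missing table could show.

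**1. Is the report planned anywhere?**
- Protocol, Outcome measures: suicidal ideas are not listed.
- Protocol, Statistical analysis: covers the primary and secondary outcomes; suicidal ideas are not mentioned.
- SAP 1.4: the PHQ-9 and GAD-7 are endpoints; suicidal ideas and item 9 are not.
- SAP 3.4: the PHQ-9 is defined only as a total from 0 to 27, with no item-level variable.
- SAP 4.3 to 4.6: nothing on suicidal ideas. The by-arm look across COVID periods concerns scores on key outcomes.
- SAP 4.7: SAEs only. The conditional summary table would be labelled by group under SAP 3.5 but would still cover only SAEs.

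**2. Would the SAE listing capture it?** Only if the ideation is reported as an event and then graded serious. On collection, the protocol says: "Data collection at 3 and 9 months will be through either online i-survey, or postal follow-up, with one reminder after two weeks". Non-responders are then followed up remotely, face to face or by telephone. The screening section says what follows a positive item 9; the documents do not say whether a positive questionnaire answer at follow-up counts as an adverse event report.

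**3. Would the PHQ-9 total show it?** Under SAP 3.4 each item scores 0 to 3, so item 9 is at most 3/27 = 11% of the total. If item 9 alone moved, the mean difference could be at most 3 times the excess proportion of positive patients. Reaching the 2-point margin would need an excess of 2/3 = 67 percentage points. This bound ignores other items that may rise with ideation, so it shows only that one item is a small part of the total. Also, SAP 3.3.2 forms a total when one or two items are missing, so a total can exist without an answer to item 9.

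**4. How precise would a by-arm comparison be?**

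Inputs from SAP 2.2: target 360; 20% non-compliant and/or lost; mean cluster size 3; coefficient of variation 0.5; ICC 0.012. That ICC is borrowed from the sample size section because none is given for ideation.

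- Plan's own figure: design effect = 1 + ((0.5² + 1) × 3 − 1) × 0.012 = 1 + 2.75 × 0.012 = 1.033, as stated.
- Patients per arm: 360 × 0.8 / 2 = 144 if the whole 20% is missing; 360 / 2 = 180 if nobody is. The 20% includes non-compliers, who can still answer item 9, so 144 is pessimistic.
- Half-width of the 95% confidence interval for a risk difference, same rate p in both arms: 1.96 × √(1.033 × 2p(1 − p) / n).

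| Assumed p | n = 144 | n = 180 |
|---|---|---|
| 3% | 4.0 points | 3.6 points |
| 5% | 5.1 points | 4.6 points |
| 10% | 7.0 points | 6.3 points |

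With 144 per arm, these rates mean about 4, 7 and 14 patients per arm. Letting the ICC run from 0 to 0.05 (assumed bounds) changes the 144-per-arm range for 3% to 10% only to 3.9 to 7.4 points. At 3% the half-width exceeds the rate itself, so the normal approximation is poor there and the figure is only a rough guide.

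**The case against.** The best case against is that the documents do provide for safety, and that the missing item is an optional description.

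- **Events have a route.** The protocol's definition of an adverse event is broad enough to include new suicidal ideas. Under Safety of participants in the trial, events reported by patients or practitioners go to the Programme Manager, then at once to the Chief Investigator or a Principal Investigator. SAEs go to the independent committee, which may also review anonymised data. This stands: it would be wrong to infer that suicidality goes unmonitored. But oversight during the trial is not a by-arm result in the report.
- **Expected events.** Of relapse, section 6.4.1 says: "May occur in 10-20% of patients over the one year follow-up, requiring restarting of antidepressant. Please report as related and expected AE". A reader might infer that the listed events are non-serious by definition and so escape the listing. The text does not say that. A relapse or severe withdrawal meeting a seriousness criterion would be an SAE and would be listed; only cases short of that fall outside SAP 4.7.
- **Ethics section.** A reader might take "provided patients with suicidal ideas, psychotic symptoms, and dementia are excluded" as making absence of suicidal ideas a safety premise of the trial. That clause concerns capacity to understand the information and to consent, and says nothing about safety during withdrawal.
- **Aim.** Safety is named in the aim of the whole programme. The objectives quoted in the SAP are effectiveness and cost-effectiveness. This limits the weight of the point.
- **Item 9.** The schedule lists suicidal ideas separately from the PHQ-9, and only the screening section ties them to item 9. Reading the follow-up row as item 9 is an inference. The gap exists on either reading.
- **It can be added later.** SAP 4.6 allows exploratory post-hoc analyses. True, but SAP 1.1 says the plan exists to avoid post hoc decisions, and a safety table chosen before the results are seen is more credible.

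**Conclusion.** The point holds as a minor, cheap improvement. Suicidal ideas are scheduled at baseline and four follow-up visits, and no planned output reports them by arm after baseline. SAP 4.7 would show only ideation that is reported and graded serious, and the PHQ-9 total does not isolate it. The finding itself rests on the text and needs no assumed event rate.

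A reader might go further and infer that the primary conclusion is at risk. It is not: the non-inferiority comparison, its margin, alpha and power are unaffected.

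The likely yield is modest. No ideation rate is given, and the relapse figure of 10% to 20% over a year describes a different event. The precision of roughly plus or minus 4 to 7 points rests on assumed rates of 3% to 10%, a borrowed ICC and 144 to 180 patients per arm.

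**What to change.** Add to SAP 4.7 one descriptive table by arm, giving:

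1. at baseline, 3, 6, 9 and 12 months, the number with item 9 answered and the number (%) scoring 1 or more, using observed item 9 only and not the item-mean imputation of SAP 3.3.2;
2. among patients scoring 0 at baseline, the number assessed at follow-up and the number (%) scoring 1 or more at any follow-up visit.

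If the suicidal ideas row in the schedule is a separate question, tabulate it in the same way. Set no test and no margin. A risk difference with a 95% confidence interval for part 2 is optional.

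**Cost.** One table, with no new data collection. Counts will probably be small and intervals wide, so an unremarkable table should not be read as evidence of safety. The proportion positive at any visit also depends on how many visits each arm completes, which is why the numbers assessed must be shown.
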